**Protocol S1- Trial Protocol**

**The need for a trial:**

**1.1 What is the problem to be addressed?**

The aim of this study is to determine whether antibiotic treatment directed against *Aspergillus fumigatus* will be effective at preventing respiratory exacerbations and improving pulmonary function in patients with cystic fibrosis (CF) who are chronically colonized/infected with aspergillus. This aim will be accomplished by means of a randomized, double-blind, placebo-controlled clinical trial incorporating two parallel treatment arms.

**1.2 What are the principal research questions to be addressed?**

Primary objective: We wish to determine whether therapy with the oral antifungal antibiotic itraconazole will reduce the absolute rate of CF pulmonary exacerbations over a 24-week treatment period compared to placebo.

Secondary Objectives: To determine whether therapy with itraconazole will improve lung function and health-related quality of life over a 24-week treatment period compared to placebo.

**1.3 Background/ Why is a trial needed now?**

The airways of patients with CF harbor a unique spectrum of bacterial and fungal organisms. *Aspergillus fumigatus* is the most prominent fungal organism found in sputum samples from patients with cystic fibrosis (CF)1-3. While studies suggest that approximately 25%, and up to 50%, of CF patients have aspergillus which grows in their sputum, it is still unclear whether the organism is acting as a significant pathogen in CF patients. A small proportion (<5%) of CF patients who culture aspergillus from their sputum develop allergic bronchopulmonary aspergillosis (ABPA), a well established complication of CF lung disease 4, however the relevance of aspergillus in the 95% of patients who culture aspergillus from their sputum, but who do not develop allergic bronchopulmonary aspergillosis (ABPA), is unknown.

Currently, most investigators and clinicians consider *A. fumigatus* to be a colonizer of the airways of patients with CF, rather than a pathogen. Therefore the current standard of care is to offer these patients no anti-fungal treatments. Our hypothesis is that *A. fumigatus* is causing disease in these patients, and that the organism is not simply an innocent colonizer of diseased airways. To test this hypothesis we will assess whether the use of a well established intervention against *Aspergillus fumigatus* in chronically infected/colonized patients has a positive effect on clinical outcome parameters (rate of pulmonary exacerbations, pulmonary function, and QOL) in patients with cystic fibrosis.

***Epidemiology and Economic Burden of CF:***

Cystic fibrosis (CF) is a genetic disease caused by abnormalities in the Cystic Fibrosis Transmembrane Regulator (CFTR) protein that controls transepithelial chloride transport in the ciliated epithelium of the conducting airways. CF leads to pathologic changes in organs that express CFTR; therefore secretory cells, sinuses, lungs, pancreas, liver and reproductive tract are involved. Abnormal chloride transport across the respiratory epithelium of patients with CF is associated with increased mucus viscosity in the lungs1. The inability of CF patients to clear this thickened mucus can result in chronic, obstructive pulmonary changes, repeated pulmonary infections, and eventually death. Despite increased understanding of the disease, CF remains an incurable life- limiting condition and children and young adults still die prematurely mostly from respiratory insufficiency.

Most patients with CF ultimately succumb to chronic airway infection and inflammation and subsequent respiratory failure. In 1969, CF was primarily a disease of children and median survival in industrialized countries was only 14 years3. However today in Canada, CF is a disease of adults and children, 45% of Canadian CF patients are now older than 18, and median survival in Canada is amongst the best in the world and has increased to age thirty-seven5;6.

The incidence of CF in Canada and the UK is estimated to be one in 2,500 births5;6. Approximately 3500 Canadian patients are registered in the Canadian CF Patient Data Registry and followed in Canadian CF clinics6. However despite being an uncommon disease, it’s societal and economic burden are considerable. The disease affects children starting in infancy, and the disease is chronic and kills young and middle-aged adults7.

The health-care needs of adults with CF are enormous. Patients with CF require frequent hospitalizations for management of pulmonary infection, and hospitalization rates for patients older than 18 have increased over the past decade8. Average direct costs of healthcare services in the US for patients with CF range from $US 6,200 to $US 43,100 per year (calculated in 1996 dollars)9-12. A Canadian study of 303 CF patients calculated average direct costs for CF adults of $8,979 per year (figures adjusted to 1996 US dollars)11. Inpatient care to treat acute pulmonary exacerbations accounted for 33% of the total direct Canadian healthcare costs10. Studies of indirect costs related to incapacity to work, disability, and premature death were estimated at $US 8400 per CF patient per year11. In total, actual direct lifetime costs of CF have been estimated at $US 250,000- $US 500,000{55, 4205}. Clearly the economic burden of CF on the healthcare system, and on patients and their caregivers, is considerable.

***Chronic Fungal Infection in CF:*** As the median age of CF patients and the intensity of antibacterial antibiotic treatment increases, multi-drug resistant bacterial organisms and fungi such as *A. fumigatus* have emerged*.* Their prevalence increases with advancing age and increasing severity of lung disease. Whereas the pathophysiological role of the major bacteria, *Pseudomonas aeruginosa* and *Staphylococcus aureus* is well established, the relevance of fungi is poorly understood. Aspergillus fumigatus constitutes the major fungal organism commonly found in lower airway specimens from CF patients. Data on its prevalence vary among centres but larger series have reported a prevalence rate ranging from 21 to 46 % in sputum-producing patients13-16. A number of risk factors for *A. fumigatus* infection have been identified: *A. fumigatus* isassociated with increasing age (paralleling an increase in severity of lung disease) and appears to be more common in patients living in rural areas17;18. It has also been described to be associated with maintenance therapy with oral or inhaled antibiotics as well as long term infection with *P. aeruginosa*, although the latter two factors may be interrelated19-21. In addition, a genetic modifier in the promoter region of the IL-10 gene that increases IL-10 production has recently been found to influence the rate of *A. fumigatus* infection22.

***Prevalence of Aspergillus infection in Canadian and Australian CF Patients:*** Data from the Canadian Cystic Fibrosis Foundation registry on 3453 CF patients in 2002 indicate that *Aspergillus fumigatus* was cultured from 9% of Canadian CF patients. This is likely an under-estimate of the true overall prevalence of aspergillus infection in Canadian CF patients since: 1) some clinical microbiology laboratories do not routinely culture for fungal pathogens using mycological media and therefore these centers will report no aspergillus growing from their patients’ sputums, and 2) results were only obtained from the first sputum culture done on each patient in 2002. Many patients may be chronically infected with aspergillus, but aspergillus may not be retrieved from every sputum culture taken, because in some instances, bacteria will overgrow the culture plate and make identification of concomitant fungal organisms difficult or impossible. Thus estimation of annual prevalence of infection from a single sputum culture is bound to underestimate the true prevalence of infection with aspergillus.

Data from the Canadian CF patient registry also suggest that the prevalence of aspergillus infection varies amongst regions in Canada. Prevalence was highest in Quebec with 14% of patients culturing aspergillus from their first sputum culture in 2002, and was lowest in the Atlantic provinces where reported prevalence of infection was only 3%. Whether these prevalences reflect true prevalence rates of infection, or whether the apparent low rate of infection in Atlantic Canada reflects failure of local laboratories to culture for fungal pathogens is unclear from the data. Data is also available from the Australian CF Patient Data Registry. In 2003 there were 2350 patients listed in the registry, and 16.4% were culture-positive for *Aspergillus fumigatus*. Prevalence of aspergillus infection was similar in adults (16.2 %) and in pediatric Australian CF patients (16.6 %).

Data from individual CF centers which routinely culture for Aspergillus species is likely more accurate than registry data. Results from the Toronto adult CF clinic indicate that 115 of 326 adult CF patients (35%) had at least 2 sputum cultures positive for Aspergillus fumigatus in 2005. Similar data from the Toronto pediatric CF clinic indicate that 61 of 234 patients (26%) had at least 2 sputum cultures positive for Aspergillus fumigatus in 2005. Prevalence of infection is higher in adults compared to children and this likely reflects an increased exposure to antibiotics in adult patients and associated selective pressures for fungal colonization/infection. It thus appears that the true prevalence of chronic aspergillus infection in Canadians with CF ranges from 26-35%.

***Allergic bronchopulmonary aspergillosis (ABPA) in CF Patients:***

A subgroup of CF patients colonised with *A. fumigatus* develop allergic bronchopulmonary aspergillosis (ABPA), a diagnosis that is based on established clinical and laboratory criteria23. The Epidemiologic Study of Cystic Fibrosis studied a series of Canadian and US patients with CF who were > 4 years of age during 1993-96. Of 14,210 North American CF patients who underwent ABPA diagnostic laboratory testing, 281 (2%) received a diagnosis of ABPA. To be diagnosed with ABPA the patient must meet all of the following five CF Consensus Conference criteria:

1) Acute or subacute clinical deterioration not attributable to another etiology.

2) Serum total IgE concentration > 1000 IU/ml (2400 ng/mL).

3) Immediate cutaneous reactivity to Aspergillus (skin test wheal > 3 mm in diameter) or presence of serum IgE antibody to *A. fumigatus*.

4) Precipitating antibodies to *A. fumigatus* or serum IgG antibody to *A. fumigatus.*

5) New or recent abnormalities on chest radiography that have not cleared with antibiotics or physiotherapy.

Our clinical trial will screen potentially eligible patients for ABPA with serum IgE and an IgE RAST serologic test against aspergillus. Itraconazole has not been proven to be of benefit for CF-associated ABPA although there is some open-label trial evidence that addition of itraconazole to systemic steroid therapy in CF patients with ABPA may facilitate a decrease in corticosteroid use. Patients who screen positive for ABPA (serum IgE > 1000 IU/ml and a positive IgE RAST against aspergillus) will be randomized.

***Relevance of A. fumigatus in CF patients:***

The clinical significance of *A. fumigatus* in patients not developing ABPA is largely unknown. Infection with *A. fumigatus* in CF patients may be transient and species genotype can change during the course of the infection4;24;25. The serologic response to *A.* fumigatus in CF patients without ABPAhas been assessed in multiple studies, and these studies consistently reported elevated IgG and/or IgE antibodies in the majority of patients whose respiratory secretions contain aspergillus organisms26-33. The presence of a host antibody response to the organism would support the concept that *A. fumigatus* is not simply colonizing CF airways, but is acting as a relevant pathogen.

A recent study from Israel and the UK suggests that chronic aspergillus infection of the airways, in the absence of ABPA, may pose a significant health risk to CF patients 34. The authors describe a group of CF patients with sputum cultures positive for *A. fumigatus* who presented with respiratory deterioration that did not respond to appropriate antimicrobial treatment. Treatment with antifungal agents (itraconazole was used in 5 of 6 patients for 4-24 months) resulted in significant improvement in the patients’ clinical conditions. These data suggest that aspergillus-related bronchitis is an over-looked and largely untreated disease in CF patients. However this hypothesis has not been confirmed by a properly designed prospective clinical investigative study.

**1.4 Relevant Systematic Reviews:**

The current standard of care is to not treat this pathogen in patients who do not have ABPA or invasive fungal disease. **No prospective experimental studies have addressed the question of whether treating aspergillus in patients with cystic fibrosis will improve clinical outcomes.** **This would be the first clinical trial examining this issue.** **Therefore there are no systematic reviews on this subject.** Effective antifungal agents with an acceptable safety profile, such as itraconazole, are now available making it feasible to design an interventional study to study the effect of antifungal therapy on the course of lung disease in CF patients.

***Pulmonary Exacerbations in CF Patients Infected with A. fumigatus:***

Chronic airway infections in patients with CF generally follow a smoldering course punctuated by acute pulmonary exacerbations. Pulmonary exacerbations are characterized by worsening cough, increased sputum production and increased dyspnea35;36. Pulmonary exacerbations contribute significantly to the burden of CF disease since they have been shown to be associated with impaired sleep and neurocognitive abilities37, impaired quality of life38, and with an increased risk of short and longer-term mortality39;40.

Treatment of the majority of pulmonary exacerbations requires intravenous antibiotic therapy and provision of chest physiotherapy. The severity of illness usually necessitates hospital admission, although some less severe pulmonary exacerbations can be treated at home with intravenous or oral antibiotic therapy. Hospitalizations for pulmonary exacerbations have been shown to be associated with short-term negative effects on health-related quality of life38 and hospitalizations (which usually last 10-14 days) contribute to significant costs to the health care system11;12.

Any therapy that can potentially decrease pulmonary exacerbations would be important for patients with CF since this a decrease in exacerbation frequency would be expected to improve quality of life38, and decrease both days absent from normal activities and health-care costs. Furthermore exacerbations associated with infections worsen the progression of lung disease in these patients39. Accordingly, the frequency of exacerbations is a strong predictor of morbidity and mortality39, and a treatment that reduces exacerbations thus has major clinical relevance.

A search of the Toronto adult and pediatric CF patient data registry was undertaken for the year 2005 to identify patients who were chronically infected with aspergillus and to determine exacerbation rates in this cohort. Exacerbation was defined as hospitalization for respiratory symptoms and/or treatment with home intravenous antibiotics. Of the 115 adult CF patients chronically infected with aspergillus (ie. at least 2 positive cultures for aspergillus in 2005), 29% experienced at least one pulmonary exacerbation in the first six months of 2005 requiring IV antibiotics. In contrast, only 14% who did not culture aspergillus from their sputum had a pulmonary exacerbation during the first six months of 2005 (p < 0.01).

Of the 61 pediatric patients from the Toronto clinic who were chronically infected with aspergillus, 23% experienced at least one exacerbation during the first six months of 2005 requiring IV antibiotics. In contrast, only 9% of 142 pediatric patients in Toronto who did not culture aspergillus from their sputum had a pulmonary exacerbation during the first six months of 2005 (p < 0.01). Thus it appears from pediatric and adult data that the risk of pulmonary exacerbation is approximately two to three times higher in Canadian CF patients who are chronically infected with aspergillus compared to those who are not. Chronic infection with aspergillus may be associated with increased risk of exacerbations, either because A. fumigatus is a pathogenic organisms that directly causes exacerbations, or because chronic aspergillus infection is associated with sicker patients who are more predisposed to exacerbations.

Data from the Australian CF Registry is similar to Canadian data. 65.9% of Australian pediatric patients who were chronically infected with aspergillus were hospitalized for a respiratory exacerbation in 2003, compared to a pediatric hospitalization rate of 34.5% in those who were not aspergillus-infected (p < 0.0001). Similarly, 61.7% of Australian adults who were chronically infected with aspergillus were hospitalized for a respiratory exacerbation in 2003, compared to an adult hospitalization rate of 44.0% in those who were not aspergillus-infected (p = 0.04). In total Australians with chronic aspergillus infection had 1.23 (sd 1.44) admissions for IV antibiotics per patient-year in 2003 compared with patients who were not infected with aspergillus who had 0.74 (sd 1.25) admissions per patient-year. This corresponds to a risk ratio of 1.66, indicating that Australian CF patients who were infected with aspergillus were much more likely to require hospital admission for pulmonary exacerbations.

***Itraconazole for Treatment of Aspergillus:*** The first-line treatment for *A. fumigatus* is itraconazole, a triazole antifungal agent with a broad activity spectrum against fungi and a favourable pharmacokinetic and safety profile amongst CF patients. Itraconazole is indicated by Health Canada for treatment of invasive and non-invasive pulmonary aspergillosis in immunocompromised and non-immunocompromised patients. Itraconazole is metabolized by side-chain hydroxylation to 14-hydroxy itraconazole, and Aspergillus fungi are susceptible to both the parent drug and the hydroxylated metabolite41. The administration of oral itraconazole 2.5 mg/kg BID in patients with CF achieves steady-state concentrations in a maximum of 8 days41. Itraconazole has proven efficacy against *Aspergillus fumigatus* *in vitro* with a low rate of innate resistance. Itraconazole has been used in studies of both CF and non CF patients with ABPA42. Once daily oral therapy has proven efficacy for ABPA in non-CF patients and reduction of fungal load has been demonstrated in these studies. A randomized, double-blind trial of treatment with either 200 mg of itraconazole twice daily or placebo for 16 weeks in non-CF patients who had corticosteroid-dependent allergic bronchopulmonary aspergillosis demonstrated significant clinical responses with reductions in corticosteroid dose, serum IgE concentration, and improvements in exercise tolerance and pulmonary-function tests in 13 of 28 patients in the itraconazole group (46 percent), as compared with 5 of 27 patients in the placebo group (19 percent, P=0.04)43.

Thus far there are no clinical studies or trials that suggest superiority of other antifungal drugs (such as voriconazole) for the treatment of aspergillus infection in non-immunocompromised patients. Voriconazole is a newer drug, and is now considered the drug of choice for angioinvasive fungal infections in transplant patients and patients with hematologic malignancies. However voriconazole is not indicated for non-invasive fungal disease, and long-term 6 month treatment with voriconazole has not been studied. Furthermore voriconazole is associated with a relatively high incidence of hepatotoxicity and fatal hepatic failure, rash (including fatal Stevens Johnsons syndrome), and retinal disease including color blindness which can occur in up to 25% of treated patients. Given it’s severe toxicities, it is not feasible to use voricanazole for 6 months of chronic therapy in patients who have non-angioinvasive CF associated fungal infection.

Pharmacokinetic data providing a rationale for an itraconazole dosing strategy in CF patients are available from 2 published studies (8.9) as well as from a multi-center pharmacokinetic study performed in Europe44. These pharmacokinetic studies in CF patients demonstrated evidence for adequate fungal-killing concentrations of itraconazole in CF sputum 41;45. Itraconazole has been found to be safe and well tolerated in these pharmacokinetic studies in CF patients. It is therefore feasible to prospectively assess whether treatment with itraconazole of CF patients who are chronically infected with *A. fumigatus* but who do not have ABPA, will have a positive impact on the course of these patients’ lung disease.

**1.5 How will the results of this trial be used?**

We expect that this study will demonstrate beneficial effects of itraconazole therapy in *A. fumigatus*- infected patients with cystic fibrosis. If confirmed, this should have a positive effect on both health status and long term evolution of lung disease in patients with cystic fibrosis. Results of the study would be disseminated at international meetings, in print form, and dissemination to caregivers would also occur directly through the Canadian and US CF Foundations.

If we do see a positive treatment effect in CF patients, then this would support our hypothesis that *A. fumigatus* is causing disease, and that the organism is not simply an innocent colonizer of diseased airways. *Aspergillus* is also commonly cultured from the respiratory secretions of patients with other chronic lung diseases, such as non-CF bronchiectasis and COPD. A positive result from our clinical trial would be an impetus to conduct future clinical trials to test the hypothesis that treatment of *Aspergillus* colonization in patients with COPD and non-CF bronchiectasis might result in clinical benefits for these other patient populations as well.

**The proposed trial:**

**2.1 Study Design**

The study will be a double-blind, randomized placebo-controlled, multi-centre, clinical trial incorporating two parallel treatment arms.

**2.2 The planned trial intervention**

Patients will be randomly allocated to one of two treatment arms:

1) Daily oral itraconazole for a 24 week treatment period, or

2) Identical placebo given in matched quantities of tablets for a 24 week treatment period.

Dosing of itraconazole has been calculated to provide a daily dose of approximately 5 mg/kg/d as per CF Consensus Guidelines. Itraconazole will be given in tablets containing 100 mg each once daily by mouth, unless the dose exceeds 200 mg/day, in which case it will be given twice daily.

Patients weighing 20 to 34 kg will receive 1 tablet (each tablet containing 100 mg itraconazole or placebo) once daily

Patients weighing 35 to 54 kg will receive 2 tablets (each tablet containing 100 mg itraconazole or placebo) once daily

Patients weighing 55 to 69 kg will receive 3 tablets (each tablet containing 100 mg itraconazole or placebo) divided into 2 doses (2 in the morning and one at night)

Patients weighing 70 kg or more will receive 4 tablets (each tablet containing 100 mg itraconazole or placebo) divided in two equal doses

Itraconazole or placebo will be taken after eating in the morning and in the evening. The drug will be taken with orange juice or 8 oz of a cola beverage (Coca-Cola TM) in order to maximize oral absorption. Absorption of itraconazole can be reduced in patients taking medications which suppress gastric acid production, and patients will be asked to take any prescribed proton pump inhibitors or H2-antagonists at lunchtime to avoid interference with absorption of itraconazole. All study patients will otherwise continue standard therapy for their CF as prescribed by their treating physician.

**2.3 Randomization Method:** Patients will be seen in the CF clinic after they have had their screening bloodwork and they will be reviewed to determine if they meet study eligibility criteria. Those who meet the inclusion criteria will be randomized after informed consent is obtained. The randomization process will consist of a computer-generated random listing of the two treatment allocations blocked by variable blocks of two or four and stratified by site. Randomization will be through central allocation of a randomization schedule and will be coordinated by the Ottawa Health Research Institute. Itraconazole or placebo study medications will be dispensed by the site research pharmacist according to the patient’s randomization assignment.

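### The 20–34 kg band, and the top of the 35–54 kg band, do not deliver the stated dose of about 5 mg/kg/day, and the morning-and-evening instruction is not limited to the patients on divided doses

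*Protocol*

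**What the plan says.** Section 2.2 of the protocol opens with the dose the schedule is meant to achieve: "Dosing of itraconazole has been calculated to provide a daily dose of approximately 5 mg/kg/d as per CF Consensus Guidelines". It then gives a frequency rule, under which 100 mg tablets are taken once daily unless the total is above 200 mg/day, and twice daily if it is. Four weight bands follow. For the lightest patients the line reads: "Patients weighing 20 to 34 kg will receive 1 tablet (each tablet containing 100 mg itraconazole or placebo) once daily". The other three, in summary, are:

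- 35–54 kg: two tablets (200 mg), also once daily
- 55–69 kg: three tablets (300 mg), two of them in the morning and the third at night
- 70 kg and above: four tablets (400 mg), split equally between two doses

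The next paragraph of section 2.2, which goes on to beverages and the timing of acid-suppressing drugs, begins: "Itraconazole or placebo will be taken after eating in the morning and in the evening". It names no weight band. The inclusion criteria in section 2.5 set the minimum weight at 20 kg and the minimum age at 6 years. Section 2.15 plans a subgroup analysis of patients under 18.

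**The concern.** The protocol presents the bands as the result of a calculation aimed at one figure, so the figure can be checked against the bands. If the lightest patients receive well under it, the protocol misdescribes the treatment tested in them. A reader comparing results in light and heavier patients would wrongly assume a similar dose per kilogram.

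The timing sentence is a separate matter. Read literally it tells every patient to take study drug twice a day, whereas the band lines tell everyone under 55 kg to take it once. A site following the text has no rule for which statement governs.

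**Working it through.** **Inputs, all from section 2.2 unless noted.** Target about 5 mg/kg/day; tablet strength 100 mg; 1, 2, 3 and 4 tablets a day in the four bands; minimum weight 20 kg (section 2.5). The top band has no upper limit, so 100 kg is used as an illustrative end point (assumption).

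**Dose delivered.** mg/kg/day = 100 × tablets per day ÷ weight in kg.

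| Band | mg/day | At lower limit | At upper limit | Mean over whole-kg weights | Weight giving exactly 5 |
|---|---|---|---|---|---|
| 20–34 kg | 100 | 100/20 = 5.00 | 100/34 = 2.94 | 3.80 | 20 kg |
| 35–54 kg | 200 | 200/35 = 5.71 | 200/54 = 3.70 | 4.57 | 40 kg |
| 55–69 kg | 300 | 300/55 = 5.45 | 300/69 = 4.35 | 4.86 | 60 kg |
| 70–100 kg | 400 | 400/70 = 5.71 | 400/100 = 4.00 | 4.76 | 80 kg |

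The stated figure is therefore reproduced in the two upper bands and over most of 35–54 kg, but not in the lowest band. The shortfall is (5 − 2.94)/5 = 41% at 34 kg and (5 − 3.70)/5 = 26% at 54 kg. Between 34 and 35 kg the dose steps from 2.94 to 5.71 mg/kg/day.

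**How much tolerance is allowed?** The protocol puts no number on its approximation, so the tolerance is an assumption. The weight above which the dose falls below the tolerance is the daily mg divided by the lower limit:

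- ±20% (lower limit 4.0): 100/4 = 25 kg in the first band; 200/4 = 50 kg in the second.
- ±25% (lower limit 3.75): 100/3.75 = 26.7 kg; 200/3.75 = 53.3 kg.
- ±30% (lower limit 3.5): 100/3.5 = 28.6 kg; 200/3.5 = 57.1 kg, so the whole second band passes.

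The upper part of the first band fails under all three. The second-band shortfall depends on the tolerance. The 55–69 kg band passes throughout, and the top band passes up to 100 kg.

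**Does whole-tablet rounding explain it?** If 5 mg/kg were rounded to the nearest 100 mg, the count would move from n to n + 1 tablets where 5w = 100n + 50, that is w = 20n + 10: at 30, 50 and 70 kg. The protocol moves at 35, 55 and 70 kg. Nearest-tablet rounding can never leave more than 50 mg/day between target and dose. The actual gaps are:

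- 31 kg: 155 − 100 = 55 mg; 34 kg: 170 − 100 = 70 mg
- 51 kg: 255 − 200 = 55 mg; 54 kg: 270 − 200 = 70 mg

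Rounding thus accounts for 20–30 kg and 35–50 kg, but not for about 31–34 kg and 51–54 kg. (Above 90 kg the gap also passes 50 mg, but the dose per kilogram stays at 4.0 or more up to 100 kg.) This is a test of the stated calculation only, not a suggested dose.

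**Timing.** The frequency rule and the four band lines agree with one another: 100 and 200 mg once daily, 300 and 400 mg in two doses. The one sentence that does not fit is the unrestricted morning-and-evening instruction, and it conflicts only with the two bands under 55 kg.

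**The case against.** The best defence is that the protocol promises only an approximate dose and works in whole 100 mg tablets, so some spread is unavoidable. Much of this stands. For a 25 kg patient one tablet gives 4.0 mg/kg and two would give 8.0, so one is the nearest available amount to the protocol's own figure. The lowest band is never above 5 partly because patients under 20 kg are ineligible. A reader might infer that the bands as a whole miss the stated dose; the table does not support that. What the defence does not cover is about 31–34 kg and 51–54 kg, where the bands depart from the stated calculation by more than tablet rounding.

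On timing, the sentence comes straight after the divided-dose bands, states no tablet count and introduces advice on food and absorption. With a single tablet in the lowest band, it can hardly be meant as a second regimen there. A reader might infer that the regimen itself is contradictory, but the frequency rule and every band line agree. What stands is that one sentence is written for all patients and cannot apply to all of them.

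It can also be said that serum itraconazole is measured at 12 and 24 weeks. Section 2.12/2.13 uses those levels to judge compliance by whether drug is detectable, and that criterion would not show a lower dose per kilogram.

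**Conclusion.** The point holds in a limited form. The stated dose is not what the first band delivers over much of its range (5.0 down to 2.94 mg/kg/day), and the second band falls to 3.70 at its top. The arithmetic is exact. Calling the upper part of the first band discrepant is robust to a tolerance of 20% to 30%; the second-band shortfall disappears at 30%. The timing sentence contradicts the once-daily bands as written and needs a qualifier.

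Several stronger conclusions might be drawn, and the protocol does not support them:

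- **Diluted treatment effect, or a confounded under-18 subgroup.** No weight distribution is given, so the number of patients affected is unknown, and mg/kg is not serum exposure. Treatment is randomised within the under-18 group, and section 2.15 calls the subgroup analyses primarily hypothesis-generating. The narrower point is one of description: light patients, who are likely to be mostly younger (an assumption), should have their results read against the dose they received.
- **Pharmacokinetic support only for twice-daily dosing.** The statement in section 1.4, "The administration of oral itraconazole 2.5 mg/kg BID in patients with CF achieves steady-state concentrations in a maximum of 8 days", concerns time to steady state. The same paragraph reports efficacy of once-daily therapy for allergic bronchopulmonary aspergillosis in patients without CF.
- **Patients falling between bands.** Limits such as 34 and 35 kg are ordinary whole-kilogram notation.

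Sample size, alpha and the primary analysis do not depend on this point.

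**What to change.** The sponsor should make three changes to section 2.2:

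1. Reconcile the statement of about 5 mg/kg/day with the weight bands.
2. Reconcile the morning-and-evening sentence with the once-daily bands under 55 kg, so that each band has one unambiguous instruction.
3. State the range the bands actually deliver (about 2.9 to 5.7 mg/kg/day for 20–100 kg if they stand as written), so that results in lighter patients can be read against it.

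Which dose or schedule is right is for the sponsor's clinical lead, and this review takes no position on it. If only the wording changes, the cost is a protocol clarification and matching text in the pharmacy instructions, with no effect on the number of patients or on the analysis.
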